#### 1.7 Schedule of Data Collection

*eTable 1: Schedule of outcomes to be assessed*

| Survey                                                                | Baseline | Post-clinic/within 2 days of intervention delivery | 90-day follow up |
|-----------------------------------------------------------------------|----------|----------------------------------------------------|------------------|
| Baseline demographic information                                      | X        |                                                    |                  |
| Satisfaction with care (7 – point Likert scale)                       |          | X                                                  |                  |
| Medication adherence                                                  | X        |                                                    | X                |
| Motivation to maintain adherence to AF therapy (7-point Likert scale) | X        | X                                                  | X                |
| AF Knowledge (Jessa AF Knowledge Questionnaire)                       | X        | X                                                  | X                |

## 2. Patient Population

The study population will be patients with confirmed AF on an electrocardiogram presenting to Westmead Hospital for clinical care. This includes both inpatients and outpatients.

### 2.1 Inclusion criterion

#### Inclusion

- Adults aged 18 years and over
- Atrial fibrillation or atrial flutter diagnosed on electrocardiogram

7. CHA2DS2VASc > 0 and/or currently prescribed anticoagulation therapy
8. Have an email address or active mobile number

## Exclusion

4. Too unwell (physically or mentally) to participate in surveys
5. Previously allocated to either condition of the study
6. Insufficient English to understand video content or to participate in the audit surveys

## 3. Analysis

### 3.1 Analysis Principles

#### General methodology

All statistical tests will be two-tailed, and a 5% significance level adopted throughout.

Analyses will be performed according to the principal of intention to treat and will include all randomised patients.

Summaries of continuous baseline variables will be presented as means and standard deviations together with medians and inter-quartile ranges. Categorical variables will be presented as frequencies and percentages. All

continuous data will be checked for normality

Methods for handling missing data are described in 3.2 – sensitivity analysis. If 80% of survey data is available, missing data will be imputed. Participants with less than 80% of outcome data available for a given survey will be removed from analysis.

Baseline values of the analysed parameter will be used as a covariate for analysis that support covariates, if these are not available see approach described below.

Balance in baseline risk factors will be considered between intervention and control groups, and if significant differences exist, additional regression analysis of outcome variables adjusting for this difference will be performed.

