### **10.3 Consent**

The study consenting documents are displayed in appendix 1. Potential participants will only be included in the study after reading and acknowledging the participant information form. This form outlines the pertinent details of the study to potential participants, including:

- Randomisation between intervention and control (1:1)
- Storage of data and data security/de-identification
- Access to patient data relevant to the study
- Right to receive treatment regardless of participation
- Right to withdraw from the study
- Consent to follow up phone contact from study coordinators at 90 days

Participants will be provided the study participant information form and contact details of relevant HREC staff and study investigators.

Investigators have developed the study information form and consent process such that pertinent study details can be communicated to participants in a way that respects their time whilst recognizing their right to understand the research they are agreeing to participate in and provide informed consent.

Study staff will also explain the details of the study and be available to provide additional information about the study to participants who request. All participants are free to withdraw from the study at any time. If withdrawal occurs, relevant study staff will not collect additional data, although data already collected will be retained to ensure the results of the research project can be measured properly and to comply with law. Data collected by the sponsor up to the time of withdrawal will form part of the research project results. If a patient doesn't want this to occur, they must tell the research team prior to joining the research project.

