### 3.2 Sensitivity Analysis

If there are more than 10% of values missing for any primary or secondary outcome, a sensitivity analysis will be conducted using a logistic regression with the outcome being missing or not and exploring any associations with demographic and medical baseline variables to understand any biases that the missingness may introduce.

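### The SAP promises an analysis of all randomised patients but drops everyone lost before day 90 from the primary analysis, and no planned analysis tests what that does to the treatment effect

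*Combined protocol and SAP*

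**What the plan says.** SAP 3.1 (General methodology) sets four rules:

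- Analysis set: "Analyses will be performed according to the principal of intention to treat and will include all randomised patients".
- Partly completed surveys: "If 80% of survey data is available, missing data will be imputed". No imputation method is named.
- Surveys below that level: "Participants with less than 80% of outcome data available for a given survey will be removed from analysis".
- Cross-reference: "Methods for handling missing data are described in 3.2 – sensitivity analysis".

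SAP 3.2 applies when more than 10% of values are missing for a primary or secondary outcome. Its whole content is that "a sensitivity analysis will be conducted using a logistic regression with the outcome being missing or not", with demographic and medical baseline variables as predictors.

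The primary analysis in SAP 3.1 is an ANCOVA of the 90-day JAFKQ on arm, age, gender, education and AF subtype, with the baseline score where available. An unadjusted t-test is also planned. SAP 1.6 allows for 15% attrition. SAP 1.7 schedules the JAFKQ at baseline, post-clinic or within 2 days (day 2 below), and day 90. Protocol 10.3 says that after withdrawal "data already collected will be retained to ensure the results of the research project can be measured properly".

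**The concern.** The first and third rules cannot both hold for a participant who does not return the 90-day survey. Followed as written, the removal rule wins and the primary comparison is between completers. The section cited for the method supplies none, because a regression of missing yes or no on baseline variables does not estimate a treatment effect.

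Drop-out could plausibly differ by arm. Participants know their allocation (Protocol 3.4), and only the video arm receives weekly links (Protocol 4). If those who leave one arm differ in knowledge from those who leave the other, the completer difference is biased. The report would contain no re-estimate to show by how much. If the conflict stays open, the choice of who enters the primary analysis may be made after the data are seen.

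**Working it through.** **1. The plan's own power figure.** Inputs from SAP 1.6: 100 per arm, 15% attrition, SD 18, difference 8.95, two-sided 5%.

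- Completers per arm: 100 × 0.85 = 85. SE = 18 × √(2/85) = 2.761. 8.95/2.761 − 1.960 = 1.28, so power is 0.900, as stated (0.897 with the t distribution).
- All 100 per arm: SE = 18 × √(2/100) = 2.546, and power is 0.940.

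The power statement therefore reproduces on completers only.

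**2. How often the gap matters.** The expected number missing is 200 × 0.15 = 30. If each of 200 participants has a 15% chance of being missing, the probability of 21 or more missing (the 10% trigger) is 0.97. Reaching SAP 3.2 is the expected case.

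**3. What the 80% imputation rule covers.** Under Protocol 5, a participant has 8, 13 or 16 applicable JAFKQ items, depending on anticoagulant treatment. Having 80% of them allows 1, 2 or 3 missing items. The rule fills in stray items and does not reach anyone lost to follow-up.

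**4. Bias of the unadjusted completer difference.** Let m be the share missing in an arm and s the number of points by which missing participants score below completers in that arm. Then bias = m_T·s_T − m_C·s_C. At 15% missing in both arms this is 0.15 × (s_T − s_C). The gaps below are assumed; the rejection rate is for no true effect.

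| Gap s_T − s_C | Bias (points) | Share of 8.95 | Two-sided 5% test rejects |
|---|---|---|---|
| 0 | 0 | 0% | 5% |
| 5 | 0.75 | 8% | 5.8% |
| 10 | 1.5 | 17% | 8.4% |
| 18 | 2.7 | 30% | 16.5% |

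**5. Bias of the completer ANCOVA, by simulation.** Assumptions not in the documents: JAFKQ correlations of 0.6 (baseline, day 2), 0.5 (baseline, day 90) and 0.7 (day 2, day 90), and drop-out log-odds rising by 1.0 or 1.5 per SD of lower day-2 score. SD is 18, with 100 per arm, no true effect and 3,000 to 4,000 trials per scenario.

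| Missing, video/control | Drop-out follows day-2 score in | ANCOVA bias | Type I error |
|---|---|---|---|
| 15%/15% | video arm only | about +1.0 | about 7% |
| 20%/10% | video arm only | +1.2 to +1.7 | about 8% to 11% |
| 15%/15% | both arms alike | about 0 | about 5% |
| 20%/10% | both arms alike | +0.6 to +0.85 | about 6.5% |

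In the video-arm-only scenarios the unadjusted t-test is worse: +1.65 at 15%/15%, and +2.17 and +2.83 at 20%/10%. Regression imputation by arm from baseline and day-2 scores brings the bias close to zero. Its empirical SD is 2.34 to 2.36, against 2.38 to 2.40 for completers, so precision is not lost.

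**6. How robust a positive result would be.** With 85 per arm, the observed difference must exceed about 1.974 × 2.761 = 5.45 points. Holding the SE fixed at 15% missing:

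- An observed 8.95 loses significance if missing video participants fall (8.95 − 5.45)/0.15 ≈ 23 points further below their completers than missing controls do.
- An observed 6.5 needs only (6.5 − 5.45)/0.15 = 7 points.

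**The case against.** Several points on the other side stand.

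- A reader might infer that the primary result has no protection at all. The documents do not support that. The ANCOVA adjusts for baseline JAFKQ and four covariates, and is valid if missingness depends only on arm and those variables. The exposure is to drop-out driven by the day-2 or unobserved 90-day score.
- A reader might infer that nothing planned would reveal a problem. eTables 2 and 4 report loss to follow-up and missing surveys by arm, so unequal drop-out would be visible. They do not show its effect on the estimate.
- Removal is per survey. A participant who misses day 90 stays in the day-2 and satisfaction analyses.
- The larger bias figures need low scorers to leave the video arm only. Nothing in the documents supports that pattern or its direction, and drop-out by high scorers would reverse the sign.
- The near-zero bias after imputation is favourable by construction. Drop-out was generated from the day-2 score and then imputed from a fully observed day-2 score. Participants lost before day 2 gain less.
- An effect of the planned size would be fairly robust at 15% missing.

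None of this removes the conflict in SAP 3.1 or supplies a re-estimated effect. How robust the result is depends on a difference not yet known, which is why the check must be specified beforehand.

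**Conclusion.** The concern holds in this form. As written, the primary analysis is a completer analysis described as intention to treat, and the section cited for missing data neither handles them nor tests the result against them. That much rests on the text alone and is firm.

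The size is less certain. Under the assumptions above, the ANCOVA bias runs from about 0 to +1.7 points, at most about 19% of the 8.95-point target (1.7/8.95), with type I error up to about 11%. The documents give no data to choose among the scenarios. A reader might go further and conclude that the result will be biased in favour of the videos, or that the sample size is wrong. Neither follows: the direction is unknown, and the stated 90% power reproduces on 85 per arm. The grade is should-fix.

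**What to change.** 1. **SAP 3.1, 80% rule.** Keep it only to decide whether a survey can be scored from its items, and name the item-level imputation method. Treat a survey below the threshold as missing; do not remove the participant.
2. **Primary analysis.** Estimate the 90-day effect in all randomised participants by multiple imputation, done separately by arm, from baseline JAFKQ, day-2 JAFKQ where available, and the ANCOVA covariates. Follow it with the planned ANCOVA. Report the completer ANCOVA as supportive.
3. **Secondary outcomes.** Build each imputation model on the measurements that outcome has. Satisfaction has no baseline value and adherence has no day-2 value. A response that the patient takes no AF medication is not missing data and must not be imputed.
4. **SAP 3.2.** Keep the logistic model as description. Add a delta-adjusted tipping-point analysis of the primary effect, with the range of deltas justified in the SAP.

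The cost is SAP wording and some programming. No new data are needed, because the baseline and day-2 scores are already scheduled and data collected before withdrawal are kept. The sample size is unchanged. The downside is a slightly more complex analysis that assumes data are missing at random given the observed scores; the tipping-point analysis is there to test that assumption.

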#### **Primary outcome analysis:**

The primary outcome will be analysed utilising an analysis covariance (ANCOVA), with age, gender, education and subtype of AF incorporated as covariates. Where baseline data are available, this will also be incorporated into the model as a covariate. An unadjusted two-tailed t-test will also be performed. We will report p-values and 95% confidence intervals.

#### **Secondary outcome analysis:**

The significance of any difference between proportional secondary outcomes (satisfaction with clinical care, motivation to maintain adherence, actual medication adherence) will be analysed using a log binomial model adjusting for age (continuous), gender (male vs female), education (year 11 and above vs less than year 11), subtype of AF (categorical). A relative risk, 95% confidence interval and p-value will also be reported. Where baseline results are available, the corresponding baseline value results (e.g. discrete total score) will also be included as a covariate. Where this does not converge, a robust poisson will be fitted.

An unadjusted chi squared test will also be calculated with a corresponding relative risk, 95% confidence interval and p-value.

### 3.2 Sensitivity Analysis

If there are more than 10% of values missing for any primary or secondary outcome, a sensitivity analysis will be conducted using a logistic regression with the outcome being missing or not and exploring any associations with demographic and medical baseline variables to understand any biases that the missingness may introduce.

### 3.3 As Treated Analyses

We will also perform an as treated analysis examining all primary and secondary outcome variables with respect to their engagement with the study intervention. Highly engaged participants will be those that watched study videos on 3 or more occasions, moderately engaged participants those who watched study videos on 1-2 occasions and poorly engaged participants those who did not watch study videos.

### 3.4 Summary of Patient Disposition

*eTable 2: Summary of Patients Disposition*

|  | Control
N C (%) | Intervention (Toal)
N T (%) |
|--|-------------------------------|-------------------------------------------|
|  |                               |                                           |

|                                     |                      |                      |
|-------------------------------------|----------------------|----------------------|
| Patients randomised          | n/N C (%) | n/N T (%) |
| Lost to follow-up at 2 days  | n/N C (%) | n/N T (%) |
| Lost to follow up at 90 days | n/N C (%) | n/N T (%) |
| Withdrew consent*            | n/N C (%) | n/N T (%) |

\*Details on reasons for consent withdrawal will be summarised as shown in etable 3

*eTable 3: Summary of Withdrawal Reasons*

| Patient Id | Treatment group | Discontinued/ withdrawn consent | Reason |
|-------------------|------------------------|----------------------------------------|---------------|
| 2                 | Intervention    | Discontinued                    |               |
| 111               | Control         | Discontinued                    |               |
| 300               | Intervention    | Withdrawn consent               |               |

### 3.5 Data Completeness and distribution

#### 3.5.1 Data available for endpoint analysis

All the data available for endpoint analysis will be presented as shown in etable 4.

*eTable 4: Data completeness for endpoint analysis*

| Outcome                     | Control
NC | Intervention (Total)
NT | Total
N |
|------------------------------------|----------------------------------|-----------------------------------------------|--------------------|
| Overall Survey completeness |                                  |                                               |                    |
| Baseline Survey             |                                  |                                               |                    |
| Inside window                      | N=x (%)                          | N=x (%)                                       | N=x (%)            |
| Outside window                     | N=x (%)                          | N=x (%)                                       | N=x (%)            |
| Missing                            | N=x (%)                          | N=x (%)                                       | N=x (%)            |
| 2 day surveys               |                                  |                                               |                    |
| Inside window                      | N=x (%)                          | N=x (%)                                       | N=x (%)            |
| Outside window                     | N=x (%)                          | N=x (%)                                       | N=x (%)            |
| Missing                            | N=x (%)                          | N=x (%)                                       | N=x (%)            |
| 90 day surveys              |                                  |                                               |                    |
| Inside window                      | N=x (%)                          | N=x (%)                                       | N=x (%)            |
| Outside window                     | N=x (%)                          | N=x (%)                                       | N=x (%)            |
| Missing                            | N=x (%)                          | N=x (%)                                       | N=x (%)            |

Inside window = 2 day survey completed within 7 days, 90-day survey completed within 120 days. Complete is defined if >80% of a survey is complete.

### 3.5.2 Data available for baseline demographic and medical history analysis

In addition, data available for baseline demographic and medical status will be presented as shown in etable 5.

*eTable 5: Baseline data completeness – Medical characteristics*

| Baseline characteristic         | Control
NP (%) | Intervention
(Total) N(%) | Total N(%) |
|---------------------------------|-------------------|------------------------------|------------|
| Medical History          |                   |                              |            |
| Sub-type of AF           |                   |                              |            |
| Atrial fibrillation             | N=x (%)           | N=x (%)                      | N=x (%)    |
| Atrial flutter                  | N=x (%)           | N=x (%)                      | N=x (%)    |
| Valvular vs non-valvular |                   |                              |            |
| Valvular                        | N=x (%)           | N=x (%)                      | N=x (%)    |
| Non-valvular                    | N=x (%)           | N=x (%)                      | N=x (%)    |
| Length of AF             |                   |                              |            |
| First AF episode                | N=x (%)           | N=x (%)                      | N=x (%)    |
| Paroxysmal AF                   | N=x (%)           | N=x (%)                      | N=x (%)    |
| Permanent AF                    | N=x (%)           | N=x (%)                      | N=x (%)    |
| Predominant flutter             | N=x (%)           | N=x (%)                      | N=x (%)    |
| Time since AF diagnosis         | N=x (%)           | N=x (%)                      | N=x (%)    |
| Comorbidities            |                   |                              |            |
| Diabetic status                 | N=x (%)           | N=x (%)                      | N=x (%)    |
| Hyperlipidaemia                 | N=x (%)           | N=x (%)                      | N=x (%)    |

|                                                    |         |         |         |
|----------------------------------------------------|---------|---------|---------|
| Hypertension                                | N=x (%) | N=x (%) | N=x (%) |
| Existing coronary heart disease | N=x (%) | N=x (%) | N=x (%) |
| Previous stroke                             | N=x (%) | N=x (%) | N=x (%) |
| Peripheral vascular disease                 | N=x (%) | N=x (%) | N=x (%) |
| Chronic kidney disease                      | N=x (%) | N=x (%) | N=x (%) |
| Number of current medications               | N=x (%) | N=x (%) | N=x (%) |
| Motivated to maintain medication adherence  | N=x (%) | N=x (%) | N=x (%) |
| Adherent to medications                     | N=x (%) | N=x (%) | N=x (%) |

CHD defined as one of the following: Prior myocardial infarction, coronary artery bypass graft surgery, percutaneous coronary intervention, or 50% or greater stenosis in at least 1 major epicardial vessel on coronary angiography.

### 3.5.3 Baseline demographic and medical maximum/minimum values

Maximum and minimum values for baseline demographic and medical characteristics will be presented as shown in etable 6. As all other variables are categorical, max/min values will only be displayed for Age, total time in clinic, and clinical assessment.

eTable 6: Demographic maximum/minimum values

| Baseline Characteristics | Control
NC (%) | Intervention
(Total)
NT(%) | Total
N(%) |
|---------------------------------|--------------------------------------|------------------------------------------------------|-----------------------|
| Age                      | Min=X,
Max=X                      | Min=X, Max=X                                         | Min=X,
Max=X       |

### 3.6 Patient Baseline Characteristics

Patient baseline demographic, medical and lifestyle characteristics will be displayed as shown below in etables 7 and 8. We will also describe the characteristics of the clinic setting and intervention delivery – including total time spent in clinic, number of videos watched, total time watching videos. Results will be tabulated and/or displayed in frequency histograms or bar graphs to demonstrate distribution.

eTable 7: Baseline Demographic and Lifestyle Characteristics by Treatment Group

| Baseline Characteristics       | Control
NC (%) | Intervention
(Total)
NT(%) | Total N(%)                   |
|---------------------------------------|--------------------------------------|------------------------------------------------------|-------------------------------------|
| Male                           | n/N C (%)                 | n/N T (%)                                 | n/N (%)                             |
| Age                            | (n=xx)
Mean (SD)
Median (IQR)  | (n=xx)
Mean (SD)
Median (IQR)                  | (n=xx)
Mean (SD)
Median (IQR) |
| Ethnicity                      |                                      |                                                      |                                     |
| Aboriginal/Torres Strait Isldr | n/N C (%)                 | n/N T (%)                                 | n/N (%)                             |
| European                       | n/N C (%)                 | n/N T (%)                                 | n/N (%)                             |

|                                                                                                       |                      |                                     |         |
|-------------------------------------------------------------------------------------------------------|----------------------|-------------------------------------|---------|
| Asian (North, East, South-East)                                                                | n/N C (%) | n/N T (%)                | n/N (%) |
| Middle-East and North African                                                                  | n/N C (%) | n/N T (%)                | n/N (%) |
| Other                                                                                          | n/N C (%) | n/N T (%)                | n/N (%) |
| Educational level                                                                              |                      |                                     |         |
| Did not attend school                                                                          | n/N C (%) | n/N T (%)                | n/N (%) |
| Attended school, did not complete 12 or equivalent                                             | n/N C (%) | n/N T (%)                | n/N (%) |
| Completed tertiary qualification (Trade certificate, diploma, bachelor or post-graduate study) | n/N C (%) | n/N T (%)                | n/N (%) |
| Number of Videos Watched                                                                       |                      | (n=xx)
Mean (SD)
Median (IQR) |         |

*eTable 8: Baseline Medical Characteristics by treatment group*

| Baseline characteristic  | Control NP (%) | Intervention (Total) N(%) | Total N(%) |
|---------------------------------|-----------------------|----------------------------------|-------------------|
| Medical History          |                       |                                  |                   |
| Sub-type of AF           |                       |                                  |                   |
| Atrial fibrillation      | n/N C (%)  | n/N T (%)             | n/N (%)           |
| Atrial flutter           | n/N C (%)  | n/N T (%)             | n/N (%)           |
| Valvular vs non-valvular |                       |                                  |                   |
| Valvular                 | n/N C (%)  | n/N T (%)             | n/N (%)           |
| Non-valvular             | n/N C (%)  | n/N T (%)             | n/N (%)           |
| Length of AF             |                       |                                  |                   |
| First AF episode         | n/N C (%)  | n/N T (%)             | n/N (%)           |
| Paroxysmal AF            | n/N C (%)  | n/N T (%)             | n/N (%)           |
| Permanent AF             | n/N C (%)  | n/N T (%)             | n/N (%)           |

|                                                    |                      |                      |              |
|----------------------------------------------------|----------------------|----------------------|--------------|
| Predominant flutter                         | n/N C (%) | n/N T (%) | n/N (%)      |
| Time since AF diagnosis                     | Median (IQR)         | Median (IQR)         | Median (IQR) |
| Comorbidities                               |                      |                      |              |
| Diabetic status                             | n/N C (%) | n/N T (%) | n/N (%)      |
| Hyperlipidaemia                             | n/N C (%) | n/N T (%) | n/N (%)      |
| Hypertension                                | n/N C (%) | n/N T (%) | n/N (%)      |
| Existing coronary heart disease | n/N C (%) | n/N T (%) | n/N (%)      |
| Previous stroke                             | n/N C (%) | n/N T (%) | n/N (%)      |
| Peripheral vascular disease                 |                      |                      |              |
| Chronic kidney disease                      | n/N C (%) | n/N T (%) | n/N (%)      |
| Number of current medications               | Median (IQR)         | Median (IQR)         | Median (IQR) |
| Motivated to maintain medication adherence  | n/N C (%) | n/N T (%) | n/N (%)      |
| Motivated to maintain medication adherence  | n/N C (%) | n/N T (%) | n/N (%)      |

CHD defined as one of the following: Prior myocardial infarction, coronary artery bypass graft surgery, percutaneous coronary intervention, or 50% or greater stenosis in at least 1 major epicardial vessel on coronary angiography.

